| 1. **Study Design**   For this study, we will use a retrospective cohort study design, looking at patients with consultations for infection and/or antibiotic prescribing between 1st April 2007 and 31st December 2015. (for an exact definition see *K. Study population* and *Error: Reference source not found*)  In a first step (Objective 1), we will describe the incidence of GP consultations for infection and the incidence of antibiotic prescribing in the main study population. This will provide important context on the burden of infection and frequency of antibiotic use in primary care.  Within the main study population, we will then undertake a nested cross-sectional study looking at all antibiotic prescriptions in the main study population. For each prescription we will use Read codes on the day of the prescription to establish the reason for the prescription. (Objective 2) This will inform our understanding of why antibiotics are prescribed.  Next, we will undertake a series of cohort studies focused on specific infectious syndromes within the main population. Three nested cohorts will be built based on a GP consultation for a) respiratory tract infection, b) urinary tract infection and c) skin/soft tissue infection. For each cohort, we will estimate the rate of infection-related adverse outcomes within 28 days of the initial GP consultation for patients with and without antibiotic treatment. (Objective 3)  In order to determine the protective effects of antibiotics against these adverse outcomes, we will then estimate the Number Needed To Treat with antibiotics (NNT) to prevent one additional adverse outcome. In particular, we will compare the NNT for patients with and without co-morbidities of interest, obesity or smoking. (Objective 4).  Finally, we will synthesize out analyses in objectives 1-4 to develop a risk model for each cohort (respiratory, urinary and skin/soft tissue models). These models will support clinical decisions and patient communication around the need for antibiotic treatment for suspected infection (Objective 5).  Results across all steps will be stratified or adjusted by age, gender, SES, ethnicity, co-morbidity, obesity and smoking status. |

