| 1. **Sample size considerations**   The main effects of interest in this study are the protective effect of antibiotic treatment (ORAB) and how this effect differs by co-morbidity (ORCO; i.e. the interaction between antibiotic treatment and co-morbidity).  Below, we derive sample sizes needed to detect these effects at 5% significance and 80% power (see Appendix Sample Size Calculation for detailed information on calculations and assumptions). We do so first for COPD patients with a respiratory infection based on previously published effect sizes. We will then relate these sample sizes to patients with other co-morbidities and with urinary or skin/soft tissue infections.  **Respiratory infections**  The power to detect any protective effects depends heavily on the risk of developing the outcome in question.  Past studies looked at a range of individual outcomes, including some extremely rare outcomes with risks as low as 0.04% (e.g. mastoiditis after URTI). They found average effect of antibiotics of ORAB = 0.69.11 and a sample size of ***971,057*** is required to detect this effect in our study.12 To be able to further investigate interactions, i.e. is the protective effect of antibiotics against rare outcomes such as mastoiditis different in patients with COPD versus no COPD, a sample size of **approx. 14 million** patients would be required.13 This is beyond the scope of this study.  Within this study, we will not consider effect sizes in rare outcomes such as mastoiditis individually. Instead, we will look at composite outcomes relevant to patients who consulted for infections, i.e. outcomes such as re-consultations, hospitalisations, etc. (see M. Exposures, Health Outcomes§ and Covariates for details). The risk for these outcomes is much more likely to be around 2.4% previously found for pneumonia.11 For this risk, required sample sizes for the protective effect of antibiotic treatment (ORAB) and how this effect differs by co-morbidity (ORCO) reduce to ***16,512***and ***258,247***.  Assuming a total sample size of at least 3,355,353 found previously (based on only 162 practices11), this study will be powered to detect ORAB and ORCO as small as 0.975 and 0.83, i.e. we will have the power to detect a protective effect of antibiotics against adverse outcomes as small as 2.5% and an increase in effects of antibiotics by 17% points in co-morbid patients.  **Urinary tract and skin/ soft tissue infections**  There are roughly 1/5 as many cases of urinary tract infection and 2/5 as many cases of skin/soft tissue infections as compared to respiratory infections.14 This translates into 671,070 cases of urinary and 1,342,141 cases of skin/ soft tissue infection. No published figures on effect sizes in urinary or skin infections could be found. Assuming similar effect sizes as in respiratory infections, the numbers for both kinds of infection well exceed the minimum sample size of 258,247 needed.  **Other comorbidities**  The powers to detect the same effects for diabetes, CKD, asthma, smoking and obesity are expected to be the same or higher, given the higher prevalence for these conditions (H. Feasibility counts). |

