| 1. **Data/ Statistical Analysis**   *1. Estimate the incidence of i) GP consultations for infection and ii) antibiotic prescriptions*  For every patient in cohort 1, data on all consultations for infection and antibiotic prescriptions occurring within the study period will be extracted. We will estimate the incidence of GP consultations for infection and antibiotic prescriptions. This will be done for all consultations and prescriptions, and then separately for each category of infection and each class of antibiotics, based on chapter 5.1 of the British National Formulary (BNF) (see Appendix Tables 1 & 2). The denominator will be estimated as total person-time contributed by patients in the cohort during the study period. We will use Poisson regression to estimate the adjusted rate of consultation and prescription, taking account of the effect of age, gender, SES, ethnicity, selected co-morbidity, smoking and obesity. Random effects will be included to take account of clustering of observations by practice. Rates will be assessed for overdispersion by additionally fitting a negative binomial model and testing for alpha greater than zero via a likelihood-ratio test. If rates are found to be overdispersed, the negative binomial model will be used instead of a Poisson model. Adjusted rate ratios will be presented with 95%-confidence intervals.  *2. Describe antibiotic prescribing patterns linked to the reason for prescription*  The overall number of antibiotic prescribing episodes will be calculated for each patient individually, counting all recorded prescriptions between 1st April 2007 and 31st December 2015. For each episode, a clinical indication will be ascertained. Read codes for a diagnosis or symptom of infection recorded on the same day as the antibiotic prescription will be assumed to represent an indication for the prescription. Where more than one possible indication within the same type of infection is recorded on the day of prescription, the more granular code will be used. If multiple indications across different types of infection are recorded, the prescription will be labelled as having multiple indications. Conversely, if no infectious indication for a prescription was found, the prescription will be labelled as having no infectious indication and we will look for any non-infectious codes associated with the date of antibiotic prescription. The ten most common indications will be established and compared to the same numbers for the period from 1998-2001.14 This approach will be replicated for each class of antibiotics based on chapter 5.1 of the BNF. Patterns of repeat consultation or prescription during episodes of infection which may be prolonged will be investigated for each antibiotic prescription extracted in objective 1. We will define a new episode as a consultation or prescription recorded at least 28 days after any previous consultation for infection or antibiotic prescription. We will undertake sensitivity analyses to investigate the impact of using different time periods to define an episode. We will also examine the use of regular (prophylactic) antibiotic treatment.  Proportions and appropriate 95%-confidence intervals will be calculated and all results will be stratified by age-group, gender, SES, ethnicity, selected co-morbidity, obesity and smoking status. Descriptive data will be displayed graphically.  *3. Estimate the incidence of adverse outcomes in the following 28 days*  For each of the selected clinical infection syndromes in the nested cohort study, events in CPRD, HES and ONS will be searched for all adverse outcomes of interest (see *M.* Exposures, Health Outcomes§ and Covariates). Crude incidence rates of for each outcome will be calculated for patients who were treated (exposed) and not treated (unexposed) with an antibiotic. The denominator will be estimated as the total person-time contributed by patients at risk of each adverse outcome, taking account of the fact that this will be different for each outcome. For example, exposed and unexposed patients cannot consult General Practice if they have been admitted to hospital and should therefore not contribute to the denominator during this period when estimating rates of GP re-consultation in the 28 days following consultation for infection. A Poisson regression model will be used to estimate adjusted rates of adverse outcomes in each group, controlling for age, gender, socio-economic status, ethnicity, co-morbidity, obesity and smoking status and assessing for interaction between age and co-morbidity. Random effects will be included to take account of clustering of observations by practice. If the outcomes are overdispersed, negative binomial models will be used instead of Poisson models. Adjusted rate ratios will be presented with 95%-confidence intervals.  *4. Estimate the number of patients needed to treat with antibiotics to avoid one infection-related adverse outcome*  For each clinical infection syndrome-related adverse outcome identified in objective 3, the odds of that outcome in the 28 days following consultation for those treated with antibiotics (unexposed) and not treated with antibiotics (exposed) will be estimated using logistic regression. We will calculate adjusted odds ratios for the protective effect of antibiotics, adjusting for age, gender, SES, ethnicity, year/season, co-morbidity and the probability of receiving antibiotic treatment (see *O. Plan for addressing confounding*) and assessing for interactions with age and co-morbidity. We will use mixed models to adjust for clustering at a practice level and to take account of clustering of observations within a patient due to repeat episodes of infection. Where there is a significant effect of antibiotics between treated and untreated patients, the NNT or NNH to prevent one individual from developing an adverse outcome is calculated as *1/(absolute risk difference)*. A significant effect will be defined by a p-value < 0.05 for the coefficients of antibiotic treatment and its interactions. To avoid an arbitrary cut-off point, p-values close to 0.05 will also be assessed but discussed separately. The NNT will then be used to assess the clinical relevance of any significant differences found. Whilst the relative risk reduction (RRR) may be similar, the NNT may be different due to differing background risk. This will be explored.  *5. Develop risk prediction tools to support clinical decision making*  For each cohort (i.e. for each of the clinical syndromes of UTI, RTI and SSTI), we will develop a logistic regression risk model to predict the risk of adverse outcomes if patients are treated versus not treated with antibiotics. Models will be developed on a random sample of 80% of the observations within a cohort, reserving 20% of the data to estimate the model’s predictive performance.  A negative outcome will be defined as the occurrence of any of the following within 28 days following the index consultation: hospital admission for infection or complication; re-consultation for infection; A&E admission; death. Antibiotic treatment will be defined as a prescription of an antibiotic on the day of consultation for clinical syndrome. Risk factors will be selected based on the analyses outlined in objectives 1-4 and broadly grouped into: socio-demographic variables, co-morbidity and clinical presentation. Biologically plausible interactions between risk factors and age and between risk factors and co-morbidities will be examined.  Whereas age and sex will be forced into the model, other risk factors will be added in order of their significance in objective 4. Risk factors will be kept in the model if they improve the predictive performance of the model as defined by model discrimination and model calibration.17 For example, a risk factor will be used in the model if it improves discrimination and/or calibration. If a variable improves discrimination but reduces calibration, it will still be included in the model, but will be omitted if it increases calibration at the cost of discrimination.  Model discrimination, i.e. the model’s ability to correctly identify patients with and without an outcome, will be estimated using the concordance (c) statistic.18 The c statistic represents the probability that between two randomly chosen patients, one with the outcome and one without, the model assigns a higher score to the patient with the outcome. As a second measure, model calibration will be assessed using the Hosmer-Lemeshow test.18 We will additionally assess model calibration graphically for reasons for poor calibration by comparing the mean observed outcome in deciles of predicted risk. In this calibration plot, the intercept indicates the extent to which predictions are systematically too low or too high, while the slope reflects overfitting of the model.  For each model, we will estimate the internal validity of discrimination and calibration estimates using cross-validation with bootstrap subsampling based on 1000 iterations. In a secondary analysis, we will assess model performance in subgroups by age, sex and co-morbidity.  Finally, we will develop a simplified scoring system using the risk factors in the model,17 assigning the total score to a specific absolute risk of adverse outcomes in the 28 days following consultation, comparing outcomes if an individual is treated versus not treated with antibiotics. We will assess the predictive performance of the risk scores using the approaches outlined above. |

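### The NNT is calculated only after a significant odds-ratio test, although Aim 4 promises an NNT comparison between risk groups without that condition

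*Protocol*

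**What the plan says.** Aim 4 (Objectives, Specific Aims and Rationale) is to estimate the NNT and compare it between each age or co-morbidity group and non-comorbid patients. The Study Design section repeats this: "we will compare the NNT for patients with and without co-morbidities of interest, obesity or smoking". Neither place attaches a significance condition.

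Section N (Data/Statistical Analysis), item 4, fits mixed logistic models with interactions for age and co-morbidity, and then makes the NNT conditional: "Where there is a significant effect of antibiotics between treated and untreated patients, the NNT or NNH to prevent one individual" is the start of the sentence that defines it as one over the absolute risk difference. The next sentence sets the condition: "A significant effect will be defined by a p-value < 0.05 for the coefficients of antibiotic treatment and its interactions". Results near the cut-off are also to be looked at and discussed apart from the rest, but how near is not said. The NNT then serves to judge the clinical relevance of differences already found significant.

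The item closes by noting that, at a similar relative reduction, "the NNT may be different due to differing background risk", and that this will be explored. No method for exploring it is given.

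The Sample size considerations section defines the group contrast as an interaction odds ratio (ORCO). The Plan for addressing confounding says that inverse probability weighting allows absolute risks and NNTs in different groups.

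**The concern.** There are two faults, and they are separate.

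**The condition.** The Study Background gives the purpose as testing whether prescribing to patients with co-morbidity could be reduced safely. For that question, a group with p>0.05 is not one without a result. Its risk difference may be compatible with a worthwhile benefit, and the interval shows how large. The rule gives such groups no NNT and no interval. Where a small stratum does pass, it passes partly because chance made the estimated benefit large, so the printed NNT tends to be too low.

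**The scale.** NNT is an absolute-risk quantity, while the coefficients tested are log odds ratios. Two groups can share an odds ratio and have quite different NNTs, or share an NNT and have different odds ratios. The named interaction test therefore does not answer the comparison in Aim 4.

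**Working it through.** **Inputs from the protocol** (Sample size considerations): "sample sizes needed to detect these effects at 5% significance and 80% power"; odds ratio for antibiotics 0.69; for the outcome risk, "The risk for these outcomes is much more likely to be around 2.4% previously found for pneumonia"; cohorts of 3,355,353 respiratory, 1,342,141 skin/soft tissue and 671,070 urinary cases.

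**Assumptions (not in the text at hand):** a two-sided test; the higher-risk group's untreated risk (5%, or 4.8% as a doubling of 2.4%); a co-morbidity share of 2%; the treated share. For the last, the protocol refers the reader elsewhere ("see Appendix Sample Size Calculation for detailed information on calculations and assumptions"), and that appendix is not at hand.

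**1. Reproduce the plan's figure.** With untreated risk p0, treated risk p1 and treated share x:

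N = (1.960 + 0.842)² × [1/(x·p1(1−p1)) + 1/((1−x)·p0(1−p0))] / (ln OR)²

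At p0 = 0.024 and OR 0.69, p1 = 0.01668. With x = 0.80, N = 16,511.4, which rounds up to the stated 16,512. The same formula at 0.04% risk gives the stated 971,057. The value x = 0.80 was found by back-calculation.

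**2. Same odds ratio, different NNT.** p1 = 0.69·p0/(1 − p0 + 0.69·p0); NNT = 1/(p0 − p1).

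| Untreated risk | Treated risk | Risk difference | NNT |
|---|---|---|---|
| 2.4% (protocol) | 1.668% | 0.732 points | 137 |
| 4.8% (assumed) | 3.362% | 1.438 points | 70 |
| 5% (assumed) | 3.504% | 1.496 points | 67 |
| 10% (assumed) | 7.121% | 2.879 points | 35 |

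The interaction odds ratio is exactly 1 in every pair, so the planned interaction test rejects only at its 5% error rate.

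**3. Same NNT, different odds ratio.** For NNT 137 at 4.8% untreated risk, the treated risk must be 4.8 − 0.732 = 4.068%. The odds ratio is then 0.841, and the interaction odds ratio is 0.841/0.69 = 1.22. The planned test would tend to flag a difference that is absent on the NNT scale.

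**4. What the condition does in a small stratum.** Take 4.8% untreated risk, OR 0.69 (true NNT 70) and equal numbers treated and untreated, all assumed.

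| Episodes | Share reaching p<0.05 | Share left without an NNT | NNT from the mean risk difference among those that pass |
|---|---|---|---|
| 1,000 | 21% | 79% | 32 |
| 2,000 | 37% | 63% | 43 |
| 5,000 | 73% | 27% | 59 |
| 10,000 | 95% | 5% | 68 |

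At 1,000 episodes the standard error of the risk difference is √[(0.048×0.952 + 0.0336×0.9664)/500] = 1.25 points. A typical interval is 1.44 ± 2.45 points, or −1.01 to 3.89. That runs from an NNH of about 99, through no effect, to an NNT of about 26. This is the information the rule withholds.

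**5. Where the condition could bind at the plan's own sizes.** If it is applied within a group, 80% power at 2.4% risk and OR 0.69 needs 16,512 episodes in that group. As a share of each cohort that is 16,512/671,070 = 2.5% (urinary), 16,512/1,342,141 = 1.2% (skin/soft tissue) and 16,512/3,355,353 = 0.5% (respiratory). An assumed 2% group in the urinary cohort has 13,421 episodes and about 71% power.

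**6. Can the NNT-scale comparison be made?** A Wald test on the difference in risk differences, with OR 0.69 in both groups, untreated risks of 2.4% and 4.8%, 80% treated and a 2% group, has about 94% power in the respiratory cohort, 60% in skin/soft tissue and 35% in urinary. With 3.6% in place of 4.8%, respiratory power is about 53%. An interval is therefore more useful than the test alone.

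**The case against.** The case on the other side has force, and it limits the point in five ways.

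- A reader might infer that the plan would report no difference when NNTs differ two-fold. The text does not say so. In the example of 137 against 67, the antibiotic effect would pass the condition easily at the planned cohort sizes, both NNTs would be calculated, and the protocol promises to explore such differences. What stands is that it names no estimate, interval or test for doing so.
- A reader might call the odds-ratio interaction the wrong test outright. It is the declared test of the hypothesis in Study Type and Sample size considerations, that the protective effect differs between groups, and it is right for a relative effect. It only fails to serve the NNT comparison in Aim 4.
- A reader might infer that all interval information is lost where p>0.05. It is not. Adjusted odds ratios, and rate ratios with 95% confidence intervals, are planned without a condition. What is withheld is the NNT and its interval.
- A reader might infer general exaggeration of NNTs. The table shows little distortion at 10,000 episodes or more, and the Amendments section already excludes the added low-power co-morbidities from NNT interpretation. Small strata and rare outcomes remain exposed.
- NNTs are not strictly confined to p<0.05, because near-misses are also considered and labelled as such. But the margin is undefined, so the boundary is not fixed in advance.

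A formal test on the absolute scale could also sit in a statistical analysis plan that is not at hand. That answers its absence here, but not the significance condition, which the protocol itself states.

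**Conclusion.** The point holds in this limited form. Section N, item 4, makes the NNT conditional on a log-odds test, while Aim 4 and Study Design promise an NNT comparison without that condition. The scale mismatch exists at any sample size: at a common odds ratio of 0.69, NNT is 137 at the protocol's 2.4% risk and 67 at an assumed 5%. The loss of NNTs and the selection towards large benefit depend on size. Both are marked at 1,000 to 5,000 episodes (27% to 79% of analyses left without an NNT; apparent NNT 59 to 32 against a true 70) and slight from 10,000.

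These figures rest on assumed risks for the higher-risk group, equal treated and untreated numbers in the small-stratum table, and independent episodes. Whether the condition applies once per outcome or within each group is unclear from the text. If it applies once per outcome, it will seldom bind for common outcomes in the large cohorts.

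**What to change.** In section N, item 4:

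1. Delete the significance condition on the NNT/NNH and the sentence about p-values near the cut-off.
2. For every syndrome, outcome and prespecified risk group, report the adjusted (weighted or standardised) absolute risk difference with its 95% confidence interval and the derived NNT or NNH, stating when the interval includes no effect. Keep the existing exclusion of the covariates added by amendment.
3. Compare groups by the difference in risk differences with its 95% confidence interval. This replaces the open promise to explore differing NNTs.
4. Keep the odds-ratio interaction as the test of the relative-effect hypothesis.

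The cost is wording and longer tables, using models and weights already planned. NNT intervals that span no effect are awkward to print, so the risk difference should be the primary column. Comparisons on the absolute scale will be imprecise for less common co-morbidities, above all in the urinary cohort, and the intervals will show this.

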| 1. **Study population**   The study period will be from 1st April 2007 to 31st December 2015.  We will perform all analyses in patients that were eligible for all linkages and fulfil the following:   1. registered at a participating English practice prior to the transfer of identifiers to the trusted third party for matching for at least a year before their entry into the study 2. their practice is deemed to be contributing ‘up-to-standard' (UTS) data at study start date 3. they had a valid identifier for linkage (NHS number for ONS mortality and HES data, postcode for IMD) 4. they had not opted out or dissented from CPRD or the linkage scheme 5. individual record is of ‘acceptable' research quality as verified by the CPRD.   **Cohort 1**: Individuals who were registered with a GP contributing to CPRD between 1st April 2007 and 31st December 2015 and who have a complete record on age, gender and IMD are eligible for inclusion in this study (see *P. Plans for addressing missing data*). Patients must have been registered with their GP for at least one year before entering the study with the exception of children aged less than one year who will be assumed to be born into the Practice. Patients can enter the study late or leave the study early in order to include patients who died within the study period (who might be inherently less healthy). Patients enter the study population on the latest of the following dates: continuous registration with GP for 12 months or 1st April 2007. Where patients registered with their GP after the 1st April 2007, patients enter the cohort after 12 months of continuous registration. Patients exit the cohort on the earliest of the following dates: the date the patient died, the date the patient left the practice, or 31st December 2015.  Subsequent studies are nested within cohort 1 (see Error: Reference source not found):   1. Nested cross-sectional study: Patients within cohort 1 with at least one prescription of an antibiotic 2. Nested cohort studies of specific infection syndromes: Patients within cohort 1 with at least one GP consultation for a specific infection syndrome (respiratory, urinary, skin/soft tissue). For these cohorts, patients will enter the cohort on the day of the consultation for infection. Patients will leave the cohort on the earlier of: 28 days after initial consultation, death, transfer out of practice or 31st December 2015. Patients can enter and exit the cohort more than once. |

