| 1. **Exposures, Health Outcomes§ and Covariates**   **§***Please note:**Summary information on health outcomes (as included on the ISAC application form above) will be published on CPRD’s website as part of its transparency policy*  *Exposure*  Exposures will include i) prescription of an antibiotic ii) GP consultation for suspected infection (see Appendices: Table 1 – Codelist for antibiotics, Table 2 – Codelist categorising indications for antibiotic use and Table 3 – Codelists to identify patients with suspected respiratory tract, urinary tract or skin/soft tissue infection)  *Health Outcomes*  The following outcomes (within 28 days of presentation in primary care) will be separately considered for analysis:   - Re-consultation for the same type of infection (CPRD; see Appendix Table 3) - Re-consultation for a side effect of antibiotic treatment (CPRD; see Appendix Table 4a –side effects of antibiotic treatment) - Complications of infection in primary or secondary care (CPRD and inpatient HES; see Appendices: Table 4b and 4c – complications of infection; depending on the indication) - Admission to Accident & Emergency (HES A&E) - All-cause hospitalisation (inpatient HES) - All-cause mortality (CPRD, HES and ONS)   We will undertake a sensitivity analysis to investigate the impact of excluding outcomes that occur on the same day as the exposure. The impact of different time windows will be explored, informed by a literature review on the natural history of the duration of different infections.  *Covariates*  We will include the following covariates:   - Age (classified as 0-4, 5-17, 18-44, 45-64, 65-84, 85-94 and 95+, years of age inclusive) - Sex (female and male) - Index of Multiple Deprivation (IMD; 1-5) - Co-morbidities (coded as indicator variables based on national guidance from Public Health England3 and feasibility1; see Appendix Table 5 for comorbidity code list)   - Diabetes   - Chronic Kidney Disease (CKD)   - Chronic Obstructive Pulmonary Disease (COPD)   - Asthma - Obesity - Smoking status15 - Season (months or quarters) and year - Ethnicity   We will undertake a sensitivity analysis of the impact of coding co-morbidities as binary indicator variable and as total number of co-morbidities. |

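### The risk models are validated only internally and never over calendar time, and whether year enters them is not fixed, so calibration of the published absolute risks for later patients is untested

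*Protocol*

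**What the plan says.** Protocol, section N (Data/Statistical Analysis), step 5, sets the split: "Models will be developed on a random sample of 80% of the observations within a cohort". The remaining fifth is the test set. The protocol adds a second step: "we will estimate the internal validity of discrimination and calibration estimates using cross-validation with bootstrap subsampling based on 1000 iterations". As a secondary analysis, "we will assess model performance in subgroups by age, sex and co-morbidity". Calendar year and practice are not among these subgroups. Calibration is to be judged by the Hosmer-Lemeshow test and a plot across deciles of predicted risk, with the plot's intercept read as the sign of systematic over- or under-prediction. The final score is mapped to an absolute 28-day risk with and without antibiotics.

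On time, section K states: "The study period will be from 1st April 2007 to 31st December 2015". Section M lists among the covariates "Season (months or quarters) and year". Objective 4 in section N estimates the treatment effect "adjusting for age, gender, SES, ethnicity, year/season, co-morbidity and the probability of receiving antibiotic treatment". For step 5, however: "Risk factors will be selected based on the analyses outlined in objectives 1-4 and broadly grouped into: socio-demographic variables, co-morbidity and clinical presentation". Only age and sex are forced in. Other factors enter in order of their significance in objective 4 and stay if they improve discrimination or calibration.

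**The concern.** The tool is meant to inform GPs' decisions about patients they will see after the data end, and what it gives them is an absolute risk. That risk depends on the model's baseline level. If 28-day outcome risk changed between 2007 and 2015, through admission practice, coding or prescribing for instance, a model without a calendar term carries the average level of the whole period.

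A random 20% has the same calendar mix as the 80%, so early over-prediction and late under-prediction (or the reverse) cancel in the overall summary. The bootstrap resamples the same mix, and the planned subgroups do not separate early from late episodes. The calibration intercept on which the plan relies would therefore sit near zero whether or not there was drift. At stake is whether the published absolute risks, and the treated-versus-untreated comparison built on them, come with evidence relevant to the patients they will be used for.

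**Working it through.** The protocol states no calibration, drift or validation figure, so there is nothing of its own to reproduce. Both checks below rest on assumed drift.

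**1. Closed form: pooled model against end-of-period risk**

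Inputs: the study period in section K runs for 9 months of 2007 plus 8 full years, so T = 8.75 years. The annual relative change in risk, d, is assumed to be 2%, 3% or 5%. Episodes are assumed evenly spread over time, with no year term in the model.

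- Pooled average level, relative to the start: m = ((1+d)^8.75 − 1) / (8.75 × ln(1+d)).
- True risk over predicted risk at the end of 2015: (1+d)^8.75 / m.

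| d per year | m | (1+d)^8.75 | ratio at end of 2015 |
|---|---|---|---|
| +2% | 1.092 | 1.189 | 1.09 |
| +3% | 1.141 | 1.295 | 1.13 |
| +5% | 1.247 | 1.532 | 1.23 |
| −2% | 0.917 | 0.838 | 0.91 |
| −3% | 0.878 | 0.766 | 0.87 |
| −5% | 0.806 | 0.638 | 0.79 |

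If the rise continued for three more years, replacing 8.75 by 11.75 in the numerator gives 1.16, 1.24 and 1.42. Over the whole period the average true risk equals m by definition, so the expected overall ratio in a random hold-out is 1.00 in every row.

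**2. Simulation: what each validation would show**

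Inputs: n = 671,070 (the urinary-infection count in the sample size section); nine equal calendar years, a 10% baseline outcome risk and two normally distributed predictors (all assumed); and an assumed annual drift on the odds. The model was fitted without year on a random 80%. For the temporal check it was fitted on the first seven years and tested on the last two. O/E is observed over expected events. CITL is calibration-in-the-large, ideally 0.

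| drift per year | CITL, random 20% | O/E, same 20%, first year | O/E, same 20%, last year | O/E, temporal hold-out |
|---|---|---|---|---|
| 0 | 0.009 | 0.98 | 1.02 | 0.995 |
| −3% | −0.005 | 1.08 | 0.89 | 0.91 |
| −5% | −0.005 | 1.18 | 0.85 | 0.83 |
| +5% | 0.010 | 0.84 | 1.20 | 1.19 |

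The overall summary in the random 20% is within about 0.01 of zero in every row, while the temporal hold-out departs from 1 whenever there is drift. The same random 20% tabulated by year also shows the drift. With no drift, all O/E values lie within about 3% of 1.

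**3. Does a year term settle it?**

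With a linear year term, the temporal O/E was 0.99, 1.04, 1.02 and 0.98 for the four rows. If drift stops after the last data year but the fitted trend is extrapolated for three years, O/E becomes 1.15 (−5% a year) or 0.89 (+5% a year). A year term helps within the period but is not a safe basis for later predictions without a check on recent data.

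**The case against.** Four points are fair, and each limits what can be said.

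- A reader might infer from the three predictor groups that the model has no calendar term. The protocol does not say so. Year and season are listed covariates and objective 4 adjusters, and step 5 draws its candidates from objectives 1-4, so year is eligible. What stands is that its inclusion is neither required nor excluded.
- A reader might infer that the reported calibration will be wrong for later patients. That depends on drift, which the protocol does not quantify. The Amendments section reports rates differing by up to 30% from earlier studies, but attributes this speculatively to country, linkage or database; it is not evidence of a trend in outcomes over time.
- A reader might infer that drift cannot be seen in a random hold-out at all. It can, if calibration is tabulated by year. The planned summaries hide it, but the data do not.
- Random splitting with a bootstrap is a recognised first stage. The protocol calls it internal validity and claims no transportability. Recalibration before use could follow later, and an analysis plan that is not shown may add calibration by period.

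The last point does not remove the concern. The protocol itself fixes how the hold-out is drawn and names the subgroups, and none of these tests time. Under the plan, the score's absolute risks come straight from models assessed in this way.

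**Conclusion.** The point holds as a gap in validation; it is not a demonstrated error in the predictions. Every assessment that step 5 fixes is internal to the same practices and years, none is by calendar time, and it is not settled whether year enters the model. Calibration of the published absolute risks for later patients is therefore untested.

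If risk drifted and year is left out, the size could matter: about 9%, 13% or 23% under-prediction at the end of 2015 for rises of 2%, 3% or 5% a year. For equal falls, true risk is 0.91, 0.87 or 0.79 of the prediction. These figures assume constant drift and evenly spread episodes. The three-years-later figures further assume that the trend continues, which no hold-out within 2007-2015 can verify. Without drift the problem does not arise. A change is worth making because the check is cheap and the tool is intended for future consultations.

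**What to change.** In step 5, choose the held-out data by calendar time, for example the latest one to two years, in place of the random 20%; or keep the random split and add the temporal hold-out as a stated validation. Report calibration-in-the-large and calibration slope in that period and by calendar year, overall and by co-morbidity. State whether year and season are candidate predictors and, if year is retained, what value is used for predictions after 2015.

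Patients can re-enter a cohort, so some will appear in both periods. Do not remove them from development because they have a later episode: that selects the development set on future survival, registration and re-infection and can itself distort baseline risk. Instead, also report hold-out performance in patients with no earlier episode.

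After validation, refit on all data and, if drift is seen, set the intercept to the most recent period before publishing absolute risks.

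Cost: no new data and little extra analysis. Reported performance may be slightly less favourable, and the latest episodes are not used in the initial development fit, although the final refit recovers them.
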